
### 2.6. Evaluation of the Change in SIC Prevalence

For three selected days, October 15, November 15, and December 15 of the years 2019–2023, at all ICUs of the participating hospitals, two types of data will be collected from the hospital information systems: (1) The total number of patients who were in the ICU on that day (00:00 to 23:59) will be documented (regardless of whether this day was during a continuous stay, at admission, or at discharge/death; the total number of patients can therefore be higher than the number of beds). (2) The total number of patients with sepsis or septic shock on that day (00:00 to 23:59) will be collected, and both SIC and SAC scores will be calculated for each patient with sepsis. The 15th of each month was chosen arbitrarily. The 4th quarter was chosen because the 4th quarter of 2019 was before the start of the coronavirus disease 2019 (COVID-19) pandemic and the 4th quarters of 2020 and 2021 (in Germany) were clearly in a pandemic wave.

### 2.7. Sample Size

It is not possible to calculate a required sample size, as to undertake this the prevalence and incidence of SIC in Austria, Luxembourg, and Germany would need to be known and this study is the first to survey these measures. The “incidence of severe sepsis and septic shock in German intensive care units” INSEP study of the SepNet Critical Care Trials Group of the German Sepsis Society served as the basis for the expected estimates of prevalence and incidence [18]. In the INSEP study, the incidence of severe sepsis and the incidence of septic shock were recorded over a period of 4 weeks in 133 intensive care units at 95 hospitals in Germany. Secondarily, the point prevalences of severe sepsis and septic shock were recorded. The study was carried out according to the definition of Sepsis-2 that was valid at the time of the study. The intensive care units participated on a voluntary basis and are not a representative sample of Germany. Almost 12,000 patients were screened, of whom around 1500 had severe sepsis or septic shock. There are currently no data on the incidence of SIC. A Japanese study found that probably 30–60% of patients with sepsis and septic shock develop SIC (depending on which scoring tool is used to make the diagnosis) [19].

The INSIC trial is very similar to the INSEP trial [18]. In contrast to the INSEP trial, the focus of the INSIC trial presented here is on determining the prevalence and incidence of SIC. The study was planned as part of the SepNet Critical Care Trials Group in close consultation with the potential study centers. No case fees can be paid out, meaning that the INSIC trial is only possible thanks to the commitment of the study centers. In order to balance the workload and benefits as well as possible, the observation period was limited to 14 days. Based on the distribution of the ICUs participating in the INSEP study, the following prognosis results are predicted for the INSIC study: Within the two-week study period of the INSIC study, around 6700 patients can be expected to be treated in the participating ICUs. Based on the figures from the INSEP study, it is concluded that around 850 [95% confidence interval, approx. 800–900] patients with sepsis and septic shock can be expected at the hospitals over 14 days. Based on the data from Japan [19], around 250–500 patients with SIC are likely to be identified. Regarding the collection of data on SIC prevalence from the years 2019–2023, the identification of approximately 2100–2200 patients per survey date can be assumed. Depending on the composition of the participating ICUs (level of care, medical specialization), possible seasonal disease clusters, and the distribution of disease severity in the participating ICUs, the SIC incidence may potentially be over- or underestimated. This could limit the validity of the data and its generalizability. These effects are attempted to be reduced by the size of the study. The possible significance of these effects can be estimated as soon as the data are available.

### 2.8. Data Collection Methods

Data collection will be carried out by the physicians/investigators of the participating ICUs. Once a day, the information required for the study is extracted from the data collected as part of standard patient care and entered into the electronic case report form (eCRF/REDCap^®^, Vanderbilt University, Nashville, TN, USA [20,21]). The investigators of the participating ICUs are responsible for ensuring that all parts of the eCRFs are filled in correctly. The completed eCRF must be approved by the investigator or by a designated sub-investigator.

### 2.9. Data Management

The Institute for Medical Informatics, Statistics and Epidemiology (IMISE, Leipzig, Germany) and the Clinical Trial Centre Leipzig (Leipzig, Germany) are responsible for creating and validating the eCRF. The data will be managed and analyzed according to the appropriate standard operating procedures (SOPs) that are valid in the IMISE/ZKS. According to §13 of the Good Clinical Practice Ordinance [22], all important trial documents (e.g., Case Report Forms (CRFs)) will be archived for at least 10 years after the completion of the clinical trial.

### 2.10. Statistical Methods

All patients who do not have SIC at the beginning of their individual observation period will be included in the calculation of the cumulative observation period for determining the incidence rate of SIC. The observation period for determining the incidence rate of SIC ends at the time of diagnosis of SIC or discharge from the ICU (depending on which event occurs first), but at the latest at the end of the 14-day observation period. The incidence rates for sepsis and septic shock are determined in the same way. To determine the incidence density, the number of incident patients is divided by the cumulative sum of the individual observation days of all patients included in the incidence calculation. The incidence density is thus calculated according to the following formula:$$\frac{\mathrm{Number}\;\mathrm{of}\;\mathrm{incidental}\;\mathrm{cases}}{\begin{array}{l} \mathrm{Sum}\;\mathrm{of}\;\mathrm{the}\;\mathrm{individual}\;\mathrm{observation}\;\mathrm{period}\;\mathrm{across}\;\mathrm{all}\;\mathrm{cases} \end{array}}$$

The corresponding 95% confidence interval is calculated based on a Poisson distribution. The incidence rates between the individual strata will be compared in pairs.

The point prevalences for SIC, sepsis, and septic shock will be determined on the first day of the observation period by calculating the ratio of the number of affected patients to the total number of patients in the ICUs on that day. The Wilson score method will be used to determine the associated 95% confidence interval. Using χ^2^ tests (or Fisher’s exact tests), the point prevalences of the individual strata will be compared. The prevalences of SIC, sepsis, and septic shock in the retrospective data collection will be determined analogously.

The available data will be described by specifying the median [interquartile range (IQR)] or the absolute (relative) frequency. Depending on the type of characteristic being analyzed, the different groups will be compared using the χ^2^ test (or Fisher’s exact test, if necessary), the Mann–Whitney U test, or the *t*-test. The Kaplan–Meier method will be used to determine survival times, and the log-rank test will be used for the relevant group comparisons.

A logistic regression model will be used to investigate mortality and describe it using odds ratios (including the associated 95% confidence intervals). Only variables that prove to be significant in the univariate analysis will be transferred to a multivariate model.

Multivariate logistic regression will be performed to compare the survival of SIC-positive and SIC-negative patients while adjusting for age, sex, the use of anticoagulants, and the SIC-adapted SOFA score at sepsis onset (i.e., the time of sepsis diagnosis). To calculate the SIC score, the SOFA score will be adapted according to Iba et al. [4] (see also Table 1). Two-sided *p* values will be used.

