## 2. Methods

### 2.1. Study Setting

The INSIC trial is a combined retrospective and prospective, multicenter, international, cross-sectional, longitudinal and epidemiological observational study. The aim of the study is to have 150 ICUs across 100 hospitals in Austria, Luxembourg, and Germany participate. The INSIC trial will be conducted by the network of the SepNet Critical Care Trials Group of the German Sepsis Foundation.

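### Both primary 95% confidence intervals treat patients as independent although they are clustered in about 150 ICUs, so the intervals are too narrow for planning trials beyond those ICUs

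*Protocol article*

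**What the plan says.** Section 2.4 lists two primary outcomes: the SIC incidence rate over 14 days, and the point prevalence of SIC on day 1 and on the retrospective reference days. Section 2.10 fixes how their uncertainty is expressed:

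- Incidence density: "The corresponding 95% confidence interval is calculated based on a Poisson distribution".
- Point prevalence: "The Wilson score method will be used to determine the associated 95% confidence interval".
- Retrospective days: "The prevalences of SIC, sepsis, and septic shock in the retrospective data collection will be determined analogously".
- Comparison of prevalences: "Using χ^2^ tests (or Fisher’s exact tests), the point prevalences of the individual strata will be compared".
- Comparison of incidence rates: "The incidence rates between the individual strata will be compared in pairs". No test is named here, and the strata are not defined anywhere.
- Sidedness: "Two-sided *p* values will be used". No significance level is stated.

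On the design, Section 2.1 says: "The aim of the study is to have 150 ICUs across 100 hospitals in Austria, Luxembourg, and Germany participate". Section 2.7 acknowledges that care level, specialty and severity mix of the participating ICUs may push the incidence estimate up or down, and relies on the size of the study to lessen this. Section 3 expects university hospitals to be over-represented. The article does not mention ICU or hospital as a cluster, overdispersion, robust variance or random effects.

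Section 2.7 also gives a planning figure: "around 850 [95% confidence interval, approx. 800–900] patients with sepsis and septic shock can be expected".

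**The concern.** A plain Poisson or Wilson interval derives its width from the total count alone. If ICUs differ in their underlying SIC rate, patients from the same ICU carry partly overlapping information about the rate in ICUs generally, and the true sampling variance exceeds the formula. Study size does not cure this: at a fixed number of ICUs, more patients per ICU makes the inflation larger.

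This matters because the product of the study is an estimate with an error bar. The Introduction says that case numbers for interventional trials cannot be calculated reliably because published prevalences scatter so widely, and that this study should supply the missing basis. Trial planners at other sites would take the interval as the plausible range for their own setting, so overstated precision passes directly into their sample sizes.

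**Working it through.** **Inputs from the article.** 150 ICUs (Section 2.1). From Section 2.7: 6700 ICU patients in 14 days, 850 with sepsis, 250–500 with SIC, 2100–2200 patients per retrospective survey date, and a source study with 133 ICUs, 4 weeks and about 1500 cases.

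**Inputs assumed.** The between-ICU coefficient of variation (CV) of the SIC rate, the intracluster correlation (ICC), and a 5% test level. The article gives none of these.

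**Step 1: the plan's own figure.** Scaling the source study gives 1500 / 133 / 2 × 150 = 846 cases, against the stated 850. Assuming independent patients:

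- Poisson: 850 ± 1.96 × √850 = 793–907.
- Binomial with n = 6700: 797–903.

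Both agree with the stated range of about 800–900, so that range contains independence variation only. Adding the sampling error of the source count, with scale factor 150/133/2 = 0.564, the variance is 846 + 0.564² × 1500 = 1323. Then 850 ± 1.96 × √1323 = 779–921.

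**Step 2: primary incidence interval.** With gamma-distributed ICU rates and μ events per ICU, the design effect is DE = 1 + CV² × μ. The actual coverage of a nominal 95% interval is 2Φ(1.96/√DE) − 1.

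| SIC cases | μ | CV | DE | Width factor √DE | Coverage | Planned interval (cases) | Clustered interval (cases) |
|---|---|---|---|---|---|---|---|
| 250 | 1.67 | 0.5 | 1.42 | 1.19 | 90% | 219–281 | 213–287 |
| 250 | 1.67 | 0.8 | 2.07 | 1.44 | 83% | 219–281 | 205–295 |
| 500 | 3.33 | 0.5 | 1.83 | 1.35 | 85% | 456–544 | 441–559 |
| 500 | 3.33 | 0.8 | 3.13 | 1.77 | 73% | 456–544 | 422–578 |

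This counts every identified SIC case as incident. Section 2.10 leaves patients who already have SIC out of the incidence calculation, so μ, and with it the inflation, may be somewhat smaller.

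**Step 3: point prevalence.** About 2150 / 150 = 14.3 patients per ICU, and DE = 1 + (14.3 − 1) × ICC.

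| ICC | DE | Width factor | Coverage |
|---|---|---|---|
| 0.01 | 1.13 | 1.06 | 93% |
| 0.02 | 1.27 | 1.13 | 92% |
| 0.05 | 1.67 | 1.29 | 87% |

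The two assumed ranges fit together. With SIC in 255/6700 = 3.8% to 510/6700 = 7.6% of ICU patients (30–60% of 850), ICC ≈ CV² × p/(1 − p) gives 0.25 × 0.038/0.962 = 0.01 at CV 0.5 and 0.64 × 0.076/0.924 = 0.05 at CV 0.8.

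**Step 4: tests.** Simulation with 150 ICUs of unequal size (CV of size 0.6) and 3000 runs gave these rejection rates for a nominal 5% χ² test with no true difference:

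| Comparison | ICC 0.01 | ICC 0.02 | ICC 0.05 |
|---|---|---|---|
| ICU-level strata, 44.7 patients per ICU (14-day cohort) | 12% | 19% | 32% |
| ICU-level strata, 14.3 patients per ICU (one day) | 8% | 9% | 16% |
| Patient-level strata within ICUs | about 5% | about 5% | about 5% |

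A comparison of two years in the same ICUs with stable ICU rates rejected in 4.5% (simulated at ICC 0.05).

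**The case against.** The best defence is that a sum of independent Poisson counts with different rates is still Poisson. If the participating ICUs are the whole population of interest, the planned incidence interval is valid; a simulation with fixed ICU rates at CV 0.8 gave 94.4% coverage. This is correct, but it does not fit the stated purpose of informing trials beyond these ICUs. Nor can the matter simply be left to an unseen analysis plan, since the article itself names the interval methods.

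Other parts of the defence stand:

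- The magnitudes rest on assumed CV and ICC values. If the ICC is 0.01 or less, the effect on a prevalence day is small.
- The figure of 14 patients per ICU divides a retrospective count by 150. Section 2.6 takes retrospective data from every ICU of the participating hospitals, which may be more than 150, and no day-1 count is given.
- A clustered variance does not repair the selection of volunteer centres, which the article discloses.

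Three stronger readings are tempting but not supported. A reader might infer that every planned strata test rejects too often. The strata are undefined, the subgroups the article does name (sepsis, septic shock, SIC, SAC grade) are at patient level, and such tests stay near 5%. A reader might also infer that using the same ICUs in each year invalidates year comparisons. No year test is specified, and shared ICUs with stable rates do not inflate one. Finally, a reader might infer that the narrow range around 850 undermines the design. It is an approximate forecast that sets no stated design choice, and the article discloses that its source used Sepsis-2. Section 2.11 adds that the source study ran largely at the same centres, so stable ICU differences are partly shared between source and target.

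**Conclusion.** The concern holds for the two primary intervals. Its direction is certain for any positive between-ICU variance once results are applied beyond the participating ICUs; its size is not, because the article gives no CV or ICC. Under the assumed ranges the incidence interval should be about 1.2–1.8 times as wide as planned, and the prevalence interval about 1.06–1.3 times. At the extreme shown (500 cases, CV 0.8), the relative half-width goes from about ±9% to ±16%. That is modest beside the prior prevalence range of 20–80%, but it means a nominal 95% interval misses roughly one time in four instead of one in twenty. Point estimates are unaffected. Excess rejection is a conditional finding: it applies only if strata are defined at ICU or hospital level. The planning range is a secondary matter of labelling.

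**What to change.** - **Incidence:** keep the point estimate. Take the 95% interval from a Poisson model with cluster-robust variance or a negative-binomial model, with log person-days as offset and ICU as the cluster, or from a bootstrap that resamples ICUs.
- **Prevalence:** use a cluster-adjusted Wilson interval (effective sample size) or GEE with ICU as the cluster, for day 1 and for the retrospective days.
- **Tests:** define the strata. For any at ICU or hospital level, use cluster-adjusted tests.
- **Reporting:** report the ICC, which later trial planners will need.
- **Data:** confirm that a coded ICU identifier stays in the data set after the full anonymization described in Section 2.18. Section 2.5 collects structural data per centre, but the article does not say that the code is kept.
- **Planning figure:** label 850 [800–900] as a projection reflecting Poisson or binomial variation only, and note that the source study's sampling error alone widens it to about 780–920.

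The cost is a change of analysis wording and retention of one code; no new data are collected. The downside is wider, less favourable intervals.

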### 1.1. Objectives

The primary outcome of the INSIC trial is the SIC incidence rate within a 14-day observation period (new cases/1000 ICU days). Moreover, we aim to determine the point prevalence of SIC on day 1 of the study period and on three reference days in the fourth quarter of each year from 2019 to 2023. The secondary outcome parameters are as follows: (I) length of stay in intensive care unit (ICU) until transfer to a normal ward; (II) ICU mortality rate (in all patients and in subgroups of patients with sepsis, septic shock, and SIC according to the different scores); (III) 28-day hospital mortality rate (in all patients and in subgroups of patients with sepsis, septic shock, and SIC according to the different scores); (IV) SIC recovery rate 72 h after SIC onset; (V) thromboembolic events after sepsis onset (in sepsis, septic shock, or SIC) up to day 28, death, or hospital discharge (whichever occurs first); and (VI) relevant bleeding without surgical trauma (non-trauma or surgery-related major bleeding causing a drop in hemoglobin of <1 g/dL) after the onset of sepsis (in sepsis, septic shock, or SIC) until day 28, death, or hospital discharge (whichever occurs first). (VII) Each of the above-mentioned outcome parameters will also be tested for correlation with the different degrees of severity of SAC (according to the SAC score) (Table 1), which allows for a more differentiated assessment of the severity of coagulopathy.

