### 2.4. Outcomes

The primary outcome parameters of the INSIC trial are as follows:
(1)The incidence rate of SIC within a 14-day observation period (new cases/1000 patient days).(2)The point prevalence of SIC on day 1 of the study period and on three reference days in the 4th quarter of each year from 2019 to 2023.

The secondary outcome parameters of the INSIC trial are as follows:
(1)Length of stay in the ICU until transfer to a normal ward.(2)ICU mortality rate (in all patients and in the subgroups of patients with sepsis, septic shock, SIC, or SAC (mild, moderate, severe) according to the different scores).(3)Mortality rate until day 28, hospital death, or hospital discharge (whatever occurs first, in all patients and in the subgroups of patients with sepsis, septic shock, SIC, or SAC (mild, moderate, severe) according to the different scores).(4)SIC and SAC (mild, moderate, severe) recovery rate 72 h after SIC or SAC onset. The time point was chosen as the 72 h period reflects a critical window during which early death in sepsis or a clinical response to sepsis therapy can be expected [15].(5)Thromboembolic events after sepsis onset (in sepsis, septic shock, SIC, or SAC (mild, moderate, severe)) up to day 28, death, or hospital discharge (whichever occurs first).(6)Relevant bleeding without surgical trauma (hemoglobin loss >1 g/dL within 24 h, due to bleeding rather than dilution) after sepsis onset (in sepsis, septic shock, SIC, or SAC (mild, moderate, severe)) until day 28, death, or hospital discharge (whichever occurs first).

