For each patient diagnosed with sepsis or septic shock during the observation period, more detailed information will be collected (date and time of sepsis onset, date and time of septic shock onset, infectious focus, causative pathogen(s), and secondary infections (super- and/or nosocomial infections and/or infections of a further organ system)). Furthermore, investigators will be asked to extract data from the hospital information system describing additional patient characteristics. These include the American Society of Anesthesiologists (ASA) classification [16], the Revised Cardiac Risk Index (RCRI) [17] score, the status of and, if applicable, the reason for pre-existing anticoagulation therapy or antiplatelet therapy, coagulopathy, and severe liver disease. Furthermore, information on past episodes of heparin-induced thrombocytopenia (HIT) type II will be collected. For all patients hospitalized with sepsis in the ICU on the first day of the observation period, it will be determined whether SIC was present before the start of the observation period. Furthermore, for each patient diagnosed with sepsis or septic shock during the observation period, on the day of sepsis diagnosis (day 0), on days 1–4, and on the day of sepsis discharge, the following measures will be collected: the sequential sepsis-related organ failure assessment (SOFA) score [2], the international normalized ratio (INR), and platelet count. For further exploratory analyses, the following parameters are recorded where available: anti-factor Xa activity, activated partial thromboplastin time (aPTT), prothrombin time, D-dimer level, fibrinogen concentration, thrombin–antithrombin complex (TAT) concentration, thrombin fragment F1.2 concentration, and measures from thrombelastometric testing. Likewise for exploratory analyses, the following parameters are collected: the levels of inflammation markers (C-reactive protein (CRP), procalcitonin (PCT), and interleukin-(IL) 6), as well as the dose of anticoagulant administered, the amount of fluid infused (per day), the amount of blood products transfused (per day), and the administered amount of coagulation factors and desmopressin (per day), determined at the same time points. Using the collected data and the SIC scores, all patients with sepsis will be tested for SIC at least once a day. Additionally, SIC scores (exact scores) will be recorded daily until day 14 after sepsis onset or discharge from the ICU (whatever occurs first). The date and time of the first SIC occurrence will be registered. The data collected will also be used to calculate the severity of SAC, according to Lyons et al. [6]. Finally, until day 14 after the onset of sepsis, each patient will be checked for thromboembolic events and non-trauma or surgery-related major bleeding (causing a drop in hemoglobin of <1 g/dL) once a day. In addition, on the 28th day after sepsis onset, it will be determined whether cardiovascular events, thromboembolic events, or non-trauma or surgery-related major bleeding (causing a drop in hemoglobin of <1 g/dL) occurred during the second 14 days of follow-up monitoring (yes/no recording for the second 14 days). Figure 2 provides an overview of the planned timeline. The time frames were chosen on the basis of balancing efforts and benefits. Since it is currently assumed that SIC occurs in the early phase of sepsis due to a dysregulation of the interaction of the innate immune response with the coagulation system, a special focus was placed on the first days, i.e., day 0 (sepsis onset) and the following 4 days. The aim is to identify possible early warning signs of SIC. Sepsis is usually treated anti-infectively for 7–14 days. The first occurrence of SIC after day 14 was considered very unlikely. The experts involved in the study planning were of the opinion that the occurrence of SIC after day 14 was most likely due to a secondary infection (which triggers a new sepsis episode) or another sepsis-independent reason. It was decided to use the 28-day mortality rate, as it is frequently collected in sepsis studies and thus allows an approximate comparison of the mortality of this cohort with other study cohorts. In the aforementioned effort to balance efforts and benefits, it was decided to investigate the potential effects of SIC on thromboembolism and bleeding risk up to day 28.

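### Bleeding and thromboembolism are compared across SIC and SAC groups only by unadjusted tests, leaving these contrasts, chiefly for bleeding, open to confounding by pre-existing anticoagulant and antiplatelet therapy

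*Protocol article*

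**What the plan says.** All references are to the protocol article.

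- **Intent.** Section 2.5 closes its rationale for the follow-up period with: "it was decided to investigate the potential effects of SIC on thromboembolism and bleeding risk up to day 28".
- **Outcomes.** Section 2.4 lists both events as secondary outcomes, to be reported by sepsis, septic shock, SIC and SAC grade: "Thromboembolic events after sepsis onset (in sepsis, septic shock, SIC, or SAC (mild, moderate, severe)) up to day 28, death, or hospital discharge" and "Relevant bleeding without surgical trauma (hemoglobin loss >1 g/dL within 24 h, due to bleeding rather than dilution) after sepsis onset". Section 1.1 adds: "Each of the above-mentioned outcome parameters will also be tested for correlation with the different degrees of severity of SAC". It names no covariates for that step.
- **Group comparisons.** Section 2.10: "the different groups will be compared using the χ^2^ test (or Fisher’s exact test, if necessary), the Mann–Whitney U test, or the *t*-test". Kaplan–Meier and log-rank methods follow, for survival times.
- **Regression.** Section 2.10 has two regression plans. One is for mortality: "A logistic regression model will be used to investigate mortality and describe it using odds ratios". The other, which also has a truncated SOFA score taken at onset among its covariates, is "to compare the survival of SIC-positive and SIC-negative patients while adjusting for age, sex, the use of anticoagulants".
- **Data on therapy.** Section 2.5 collects "the status of and, if applicable, the reason for pre-existing anticoagulation therapy or antiplatelet therapy". It also collects, for exploratory use, the anticoagulant dose given during the study.

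**The concern.** A confounder of the SIC–bleeding contrast must be related both to SIC status and to bleeding. Pre-existing anticoagulation is a clear candidate. Some anticoagulants raise INR, and Table 1 scores SIC and SAC from INR. The same drugs affect bleeding. The protocol already treats anticoagulant use as something to adjust for, but only when the outcome is survival. For the two outcomes on which these drugs act most directly, no adjusted analysis is stated, although the data will be in hand.

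Sections 1 and 3 say the results are meant to inform trials of treatments that modulate coagulation. A crude excess of bleeding in SIC or in severe SAC could be read as a consequence of the coagulopathy when part of it comes from drugs the patient was already taking.

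A smaller, linked problem is that the anticoagulant covariate in the survival model has no time point. It could mean therapy before sepsis or treatment given in the ICU, and section 2.5 records both. Treatment started after onset may itself be a response to SIC, so the two readings do not estimate the same thing.

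**Working it through.** **1. Which stated method reaches which outcome (section 2.10, with 1.1 for the SAC step)**

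| Method | Outcome | Adjusts for anticoagulants? | Adjusts for antiplatelets? |
|---|---|---|---|
| χ²/Fisher, Mann–Whitney, t-test | group comparisons in general | no | no |
| Correlation with SAC grade | each listed outcome | none named | none named |
| Kaplan–Meier, log-rank | survival times | no | no |
| Logistic model with univariate screening | mortality | not named | not named |
| Adjusted logistic model | survival, SIC-positive v SIC-negative | yes, no time point | no |

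Only the first two rows can apply to bleeding and thromboembolism.

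**2. How therapy can move a patient between groups (Table 1)**

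INR of 1.4 or more gives 2 SIC points. With a platelet count of 100 to <150/nL (1 point) the coagulation part is 2 + 1 = 3, which exceeds 2. One SOFA point then gives a total of 4, which is SIC. For SAC, the severe grade joins its two conditions by *or*, so INR of 1.6 or more is enough alone. An INR raised by a drug can therefore change the group.

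**3. Size for bleeding, with no SIC effect**

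The protocol gives no treatment frequency and no event risk, so all inputs here are assumptions. Let p1 and p0 be the proportions on pre-existing anticoagulation with and without SIC, and R the drug's risk ratio for bleeding. If SIC has no effect within treatment strata:

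crude RR = [1 + p1(R − 1)] / [1 + p0(R − 1)]

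With p1 = 0.35 and p0 = 0.20:
- R = 2: 1.35 / 1.20 = 1.125
- R = 3: 1.70 / 1.40 = 1.214

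**4. Wider range, with the protocol's group sizes**

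The projected numbers reproduce. Scaling the earlier German survey quoted in section 2.7 gives 1500 × (14/28) × (150/133) = 846 patients with sepsis (stated: about 850). Taking 30–60% of 850 gives 255–510 with SIC (stated: 250–500).

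Using 255 or 510 SIC patients out of 850, I assumed untreated bleeding risk of 5–10%, a drug odds ratio of 1.5–3 and no SIC effect. The test is a two-sided pooled two-proportion test at 5% (level assumed, as none is stated).

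| Assumed use, SIC v no SIC | Crude odds ratio | Probability that the unadjusted test rejects |
|---|---|---|
| 30–50% v 20% | 1.04 to 1.42 | about 5% to 42% |
| 20% v 40% | 0.78 to 0.92 | about 6% to 24% |

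The top of the range, as an example: untreated risk 10% and odds ratio 3 give a treated risk of 25%. Then SIC risk = 0.5 × 0.25 + 0.5 × 0.10 = 0.175 and non-SIC risk = 0.2 × 0.25 + 0.8 × 0.10 = 0.13. The crude odds ratio is (0.175/0.825) / (0.13/0.87) = 1.42.

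The bias can be negligible or material, and can go either way.

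**The case against.** The best defence has four parts.

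*The test sentence is generic.* It names neither bleeding nor thromboembolism, and an analysis plan that is not shown could contain an adjusted model. This is true, and it limits how firmly the point can be put. But the article does more than leave details open. It sets out an adjusted model with a covariate list for one outcome and leaves only crude tests for the others. Extending that model is a better method, not merely a missing detail.

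*The study is mainly descriptive.* Its aims are incidence, prevalence and recovery, and the wording on effects is cautious and appears in a justification of follow-up length. Crude event rates under routine care are legitimate output. This stands, and it is why the crude results should be kept and labelled as description. It does not cover the stated interest in what SIC does to these risks.

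*Confounding is not shown.* A reader might infer that the bleeding and thromboembolism results will be biased, and biased upwards. The documents do not support that: without treatment frequencies or event risks, neither size nor direction can be derived from them.

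*Thromboembolism is different.* It is tempting to argue that prophylaxis withheld in SIC would produce a spurious excess of thrombosis. With assumed prophylaxis of 50–70% in SIC v 90% without, and a protective risk ratio of 0.5, the crude ratio would be 0.65/0.55 = 1.18 to 0.75/0.55 = 1.36. But treatment in the ICU after onset is partly a consequence of SIC, so that excess is not simply spurious, and adjusting for baseline therapy would not remove it. I do not rely on these figures.

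**Conclusion.** The point holds in a limited form. The protocol intends to look at possible effects of SIC on bleeding and thromboembolism, states only unadjusted comparisons for them, and reserves adjustment for anticoagulant use to survival. It names antiplatelet therapy in no model, although it collects it. The crude SIC and SAC contrasts are open to confounding by pre-existing therapy, chiefly for bleeding.

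The illustrative crude bleeding risk ratio of 1.13 to 1.21 with no SIC effect rests wholly on assumed inputs: use of 35% v 20% and a drug risk ratio of 2 to 3. Other plausible inputs give almost no bias or bias in the opposite direction. The link from anticoagulants to INR and bleeding is general pharmacological knowledge, not a figure from the protocol. The primary outcomes are not affected.

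**What to change.** 1. For relevant bleeding and, if event numbers allow, for thromboembolic events, add the logistic model already planned for survival, by SIC and by SAC grade. Covariates: age, sex, SIC-adapted SOFA score at sepsis onset, pre-existing anticoagulant therapy and pre-existing antiplatelet therapy, both as at sepsis onset.
2. Report the adjusted odds ratio with its 95% confidence interval as the comparison of interest, and label the χ² or Fisher results as unadjusted description.
3. In the survival model, define the anticoagulant covariate as pre-existing therapy at sepsis onset. Report the anticoagulant dose given in the ICU after onset descriptively.

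The cost is analysis wording only, since section 2.5 already collects the therapy data. With few events, chiefly for thromboembolism, a short covariate list or a penalised model will be needed. Two limits remain. Baseline covariates do not deal with treatment changed after onset, and a logistic model does not account for follow-up that ends at different times through death or discharge. Both should be acknowledged when the results are reported.
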